### Confidentiality 

See section on data management above.

### Plans for collection, laboratory evaluation and storage of biological specimens for genetic or molecular analysis in this trial/future use 

Not applicable, since no collection, laboratory evaluation, and storage of biological specimens is planned.

### Statistical methods 

Primary estimand: Within the population of all randomized patients defined by the inclusion and exclusion criteria with at least one assessment of the LHB total score at any point in time, the primary endpoint of LHB total score at 12 months after surgery will be analyzed. The occurrence of the intercurrent events such as reoperation procedures, additional operations, or further injuries of the ipsi- or contralateral distal or proximal biceps tendon will be disregarded (treatment policy strategy). We expect a maximum of 10% of patients to experience an intercurrent event within the first 12 months after surgery. The summary measure will include the following methods: Point estimates for both treatment arms will be presented as mean and standard deviation with corresponding 95% confidence interval. To test the null hypothesis H_0_: μ_anchor_ – μ_loop_ ≥ 5 against the alternative hypothesis H_1_: μ_anchor_ – μ_loop_ < 5 (μ_anchor_, μ_loop_: mean of LHB total score after arthroscopic anchor tenodesis, loop tenodesis at month 12) at a one-sided significance level of 0.025, a generalized linear model (GLM) with the LHB score at month 12 as the dependent variable and the type of treatment and center as fixed factors and LHB score at baseline as covariate will be used. The difference between anchor tenodesis and loop tenodesis will be presented as the least squared means together with an associated 97.5% one-sided confidence interval based on the GLM. If the upper bound of the CI is not higher than 5 points, then the null hypothesis will be rejected. If non-inferiority of loop tenodesis is determined, superiority of loop tenodesis will then be tested in the same way. With an expectation of no more than 10% missing values for the LHB score at month 12, which will be considered missing completely at random (MCAR) or missing at random (MAR), multiple imputation using the Markov chain Monte Carlo (MCMC) method will be used to account for such missing values. The MCMC imputation model will include the LHB measures at 6 weeks, 6 months, and, if available, at 24 months, as well as the baseline patient characteristics age, sex, BMI, dominant hand, and further injuries. A sensitivity analysis using a GLM on ranks will be used to explore the robustness of inference from the initial model.

The 2^nd^ estimand is based on the composite policy strategy. The endpoint is the LHB total score > 80 points at 12 months after surgery as a binary endpoint. Intercurrent events as defined above will be classified as non-responders regardless of the LHB score at month 12. The summary measure will be the difference in the proportions between the two treatment arms.

The 3^rd^ estimand is based on the hypothetical policy strategy. The endpoint and the summary measure are defined according to the primary estimand, but for all patients with intercurrent events, the LHB score at month 12 will be replaced by a hypothetical score. This score is based on a multiple imputation method as for the primary estimand, using only information before the occurrence of the intercurrent event. All estimands together will provide a good answer to the question of whether the new method of loop tenodesis is non-inferior or even superior to the standard anchor tenodesis procedure. Furthermore, subgroup analyses based on age and sex will be performed. Statistical analyses of the secondary endpoints will be carried out in an exploratory manner without any multiplicity adjustments as described in detail in the Statistical Analysis Plan. Descriptive safety analyses will be provided.

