#### Primary outcome measure

The *primary endpoint* will be the biceps-specific LHB score as assessed at 12 months after surgery. The score will also be recorded at baseline and at the 6-week, 6-month, and 24-month follow-ups. This highly disease-specific assessment of LHB-associated outcome after surgery includes patient-reported symptoms (pain, cramps, or tenderness), the cosmetic result (Popeye deformity), and an objectively measurable functional parameter (flexion strength), each compared to the healthy contralateral tendon [25], with patient-reported outcome weighted more heavily in the overall score than functional outcome [25, 26]. The LHB score has been shown in previous studies to be a valuable tool for evaluating outcome after LHB tenotomy and tenodesis procedures [17, 25–30].

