
### Participant timeline

The following baseline data will be collected for each study patient after written informed consent has been obtained: age, sex, height, weight, arm dominance, American Society of Anesthesiologists (ASA) grade, concomitant diagnoses and medications, previous arm surgery, and tobacco and alcohol use. All functional outcome scores will be assessed at enrollment prior to surgery to obtain preoperative scores.

After the allocated study intervention has been conducted, patients will be seen for follow-up examinations at four postoperative visits (after 6 weeks, 6 months, 12 months, and 24 months) to evaluate the study outcome parameters (see Table 1).

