### Sample size calculation 

The primary objective of this study is to show the non-inferiority of loop tenodesis in comparison with arthroscopic anchor tenodesis with respect to the primary clinical outcome LHB score (scale range 0–100). The clinical non-inferiority margin was set at 5 points on the LHB score, which was based on statistical considerations and clinical judgment. Moreover, an expert panel of German-speaking shoulder surgeons was consulted on the study design and the choice of non-inferiority margin. The panel defined a non-inferiority margin of 5 points, taking into account the differences in LHB scores between the established procedures and the minimal clinically important differences in other related scores. For loop tenodesis to be considered standard of care and to show non-inferiority to implant-based tenodesis techniques, it has to outperform the technically easier procedure of biceps tenotomy. According to Kerschbaum et al. [26, 34], the mean LHB score of patients treated with biceps tenotomy is at least 5 points lower than that of patients treated with arthroscopic epiosseous suprapectoral anchor tenodesis. Setting the non-inferiority margin at 5 points can also be considered a benchmark for outperforming biceps tenotomy as a historical control, as suggested by studies by Kerschbaum et al. [26, 34]. Moreover, according to the literature [17, 25–28], we expect a mean LHB score of 85 with a standard deviation of 10 for both treatment groups at 12 months. The non-inferiority margin of 5 points is half of the expected standard deviation, which is widely accepted as the minimal clinically relevant difference of PROs [35]. To show non-inferiority with a non-inferiority margin of 5 points and a standard deviation of 10 points with a power of 90% at a one-sided 2.5% level of significance, a total of *n* = 172 patients are required for statistical analyses. Assuming an early drop-out rate of 10% (change of indication during arthroscopy and thus no need for surgery or no information on the clinical outcome (drop-out before week 6)), a total of *n* = 192 patients (96 per group) need to be randomized. Sample size was calculated by using SAS 9.4 and the procedure proc power.

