### Assignment of interventions: allocation 

Allocation to one of the two treatment arms in a 1:1 ratio will be randomized using block-wise randomization with different block sizes stratified by center. The randomization list and the block size will be concealed for all participants until the final endpoint has been analyzed. Randomization will be carried out using the clinical database management system (CDMS) managed by the Center for Clinical Studies at the University Hospital Regensburg. After a patient has been enrolled by signing the informed consent and on the day of surgery, the responsible personnel (investigator and/or study nurse) must use the individual login for the CDMS to randomize the patient. All randomizations will be logged and documented within the system, and predefined users such as the study monitor will be automatically informed about the randomization.

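### The primary population's one-score condition is met at baseline, so it keeps the early drop-outs that the sample size leaves out, uses up the 10% missing-data allowance, and leaves those patients to be imputed without treatment arm as the model is listed

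*Protocol article*

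**What the plan says.** The Protocol article describes the same patients in three places.

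- **Statistical methods** (primary estimand): the population is all randomised patients meeting the eligibility criteria "with at least one assessment of the LHB total score at any point in time". Missing month-12 scores are multiply imputed: "With an expectation of no more than 10% missing values for the LHB score at month 12". The imputation predictors named are the LHB scores at 6 weeks, 6 months and, where available, 24 months, plus age, sex, BMI, dominant hand and further injuries. Treatment arm and baseline LHB score are not named.
- **Sample size calculation**: 172 patients are needed for analysis. This is raised to 192 for a 10% early drop-out, made up of patients whose indication changes at arthroscopy and patients with "no information on the clinical outcome (drop-out before week 6").
- **Timing of the first score**: under Primary outcome measure, "The score will also be recorded at baseline and at the 6-week, 6-month, and 24-month follow-ups". Under Participant timeline, "All functional outcome scores will be assessed at enrollment prior to surgery to obtain preoperative scores". The allocation section places randomisation later: "After a patient has been enrolled by signing the informed consent and on the day of surgery". Table 1 likewise puts the LHB score at study inclusion, ahead of allocation.

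**The concern.** A condition of at least one score at any time normally removes patients who contribute nothing to the outcome. Here the baseline score meets it, so it does no work. The estimand section therefore keeps the patients whom the sample size section counts as lost to the analysis.

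Two things follow. First, the early drop-outs enter the primary set with a missing month-12 score, and the missing-data allowance is spent before any loss between week 6 and month 12 is counted. Second, these patients have no post-operative LHB score. Their month-12 value would be drawn from baseline characteristics, and as the predictors are listed, nothing in the model tells the arms apart. In a non-inferiority trial, anything that pulls the arms together favours the claim being tested.

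**Working it through.** **Inputs.** Margin: "The clinical non-inferiority margin was set at 5 points on the LHB score". Mean and SD: "we expect a mean LHB score of 85 with a standard deviation of 10 for both treatment groups at 12 months", so the true difference is 0. One-sided alpha 0.025, power 90%, 172 analysed, 192 randomised and 10% early drop-out come from the sample size section. At most 10% missing at month 12 comes from Statistical methods. Loss after week 6 is not stated, so 0%, 3%, 5% and 10% are assumed.

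**1. The plan's own figures.** Power for a two-sample t test comes from the noncentral t with noncentrality 5 / (10 × √(2/n)), n per arm and 2n − 2 degrees of freedom. The smallest n reaching 90% is 86 per arm, 172 in total, with noncentrality 3.28 and power 90.3%. Then 172 / 0.9 = 191.1, which gives 192 in equal arms. Both figures reproduce.

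**2. Who is in the primary set.** The baseline score precedes allocation, so the condition is met by all 192, apart from anyone whose baseline visit was incomplete. The sample size section implies 172. The difference is 192 − 172 = 20 patients.

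**3. Missing share and power.** With the 20 in the set, the share missing at month 12 is 1 − 172 × (1 − later loss) / 192. Power uses the observed scores only, with no gain from the baseline covariate or from imputation.

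| Assumed loss after week 6 | Observed scores | Missing of 192 | Power |
|---|---|---|---|
| 0% | 172 | 10.4% | 90.3% |
| 3% | 166.8 | 13.1% | 89.4% |
| 5% | 163.4 | 14.9% | 88.8% |
| 10% | 154.8 | 19.4% | 87.1% |

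Before rounding, two separate 10% losses give 1 − 0.9 × 0.9 = 19%. In that case a baseline-to-month-12 correlation of about 0.3 restores the power: the SD becomes 10 × √(1 − 0.3²) = 9.54, and 155 observed scores give 90.0%.

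**4. Does keeping the 20 change the power?** Keeping or dropping them does not alter the number of observed scores. In simulation (3,000 runs, 20 imputations, 10 of 96 missing per arm), power was 89.8% with the 20 dropped and 89.9% with them kept and imputed with arm in the model.

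**5. Effect of the listed imputation model.** Without arm in the model, imputed scores in both arms share one mean. Baseline characteristics are balanced by randomisation and cannot stand in for arm. The expected estimate of a true 5-point deficit is 5 × 172/192 = 4.48. The simulation gave 4.46, with non-inferiority wrongly declared in 3.7% of runs, against 2.5% with arm in the model. A 20,000-run repeat gave 4.47, and 3.6% against 2.5%. The simulation covers the 20 early drop-outs only and uses no baseline covariate.

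**The case against.** A reader might infer that the population clause breaks the 90% power, or that the true power is 87%. The documents do not support this. The month-12 missing figure is not an input to the sample size; only the early drop-out is. If at most 10% of 192 is taken to include the early losses, at least 172.8 scores are observed, which is what the calculation needs. The 0.4-point excess in 10.4% comes from rounding. The 87% figure needs a further 10% loss that the protocol never states. It would arise equally if the set required a post-baseline score, and it gives no credit for the planned baseline covariate or the interim scores. All of this stands.

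The imputation list also need not be complete, and the full model may be in the analysis plan, which is not shown. This stands too, so the error inflation is conditional on the list being the whole model.

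Nor is it settled that patients with a changed indication would all have imputed scores. The stopping rules remove a patient only on withdrawal of consent, so some could be followed and observed, and the estimand's reference to the eligibility criteria leaves their status unclear. The text fails to fix the point; it does not fix it wrongly.

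The mismatch itself remains. One section leaves these patients out of the analysed number, the other keeps them in, and no loss after week 6 is budgeted.

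**Conclusion.** The point holds as an inconsistency with a conditional bias, and should be settled before analysis. As written, the primary set is about 192, against the 172 implied by the sample size section. The early losses alone account for 10.4% missing at month 12, so the 10% expectation leaves no room for later loss.

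The power statement is sound for 172 observed scores. It slips to between 89.4% and 87.1% for assumed later losses of 3% to 10%, before any adjustment gain, whichever set is used.

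The more consequential effect is on validity. If the imputation model contains only the listed predictors, a deficit equal to the margin is estimated about half a point too small, and the one-sided error is about 3.7% instead of 2.5%. This assumes 10 early drop-outs per arm with no post-operative score, normal data with SD 10, and missingness unrelated to outcome. With arm in the model, the inflation disappears.

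**What to change.** 1. Delete the one-score condition and define the primary set as all randomised patients. State explicitly that patients with only a baseline score, and those whose indication changes at arthroscopy, are included.
2. Add treatment arm and baseline LHB score to the imputation model.
3. Restate the expected missing share at month 12 as the 10% early loss plus a stated later loss: up to about 19% if the two 10% figures are separate.
4. Restate power for the resulting number of observed scores (about 87% unadjusted at 19%), or state the baseline correlation, about 0.3, that restores 90%. Observing 172 scores under two separate 10% losses would otherwise need 172 / 0.81 = 212.3, or 214 randomised in equal arms.

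If the sample size section expresses the intention, require at least one post-baseline LHB score instead and present the all-randomised analysis alongside.

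The set should not be limited to patients whose indication is confirmed at arthroscopy. Randomisation takes place on the day of surgery and surgeons are not among those blinded, so that exclusion could be decided with the allocation known.

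The cost is wording in two sections and two added imputation variables, with no new data. The stated power may become slightly less favourable.

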### Interim analyses 

Not applicable, since no interim analyses are planned.

### Plans to give access to the full protocol, participant level-data and statistical code 

The statistical analysis plan will be made available as an addendum to the primary paper. Individual deidentified participant data (including data dictionaries) will be shared through Zenodo, a European open access data repository. Data and documents will be made available to interested researchers upon a reasonable request for a period of five years.

(See section on dissemination plan below).

## Oversight and monitoring

### Composition of the coordinating center the data safety and monitoring board (DSMB), and the trial steering committee 

The trial will mainly be managed by two clinical trial coordinators, who are also the principal investigators of the trial, and one additional project manager, all of whom are members of the Department of Trauma Surgery at the University Hospital Regensburg. Randomization, data management, and biometric analysis will be done by the Center for Clinical Studies (ZKS) at the University Hospital Regensburg. Each recruiting center will be represented by a cooperating investigator, who is responsible for the coordination and performance of local recruitment, randomization, patient-blinded treatment, and observer-blinded follow-up examinations. To ensure adherence to the intervention scheme and the quality of performance of each recruiting center, an independent Data Safety and Monitoring Board (DSMB) has been established, consisting of three experienced shoulder surgeons and researchers who are not involved in the conduct or design of the trial and are not part of the medical institutions involved. The Board's responsibility will be verifying the proper conduct of the study with respect to randomization, blinding, and quality of surgical techniques using the mandatory documentation during online meetings following each on-site monitoring visit by the independent study monitor. Furthermore, the Board will advise on the continuation, modification, or termination of the whole trial in the event of cumulative occurrence of adverse events of special interest and failure to meet recruitment milestones as part of the meetings. Moreover, the chairman of the Commission for Research and Development of the German, Austrian, and Swiss Societies for Shoulder and Elbow Surgery (DVSE Kommission “Research und Development”) has agreed to assume the patronage of the trial and supervise the overall progress of the study and the publication of the results. In case of structural, coordination, or organizational problems, he will advise the recruiting centers.

### Composition of the data monitoring committee, its role and reporting structure 

Quality assurance will consist of a combination of remote monitoring and on-site monitoring. Remote monitoring will be done by the data manager and will focus on data flow and accuracy in completing the eCRF. If performance falls below a predefined quality threshold, additional on-site monitoring visits will be scheduled. On-site monitoring will be commissioned to the CRO multi-service-monitoring, which has specialized in the monitoring of non-commercial IITs since 2000. The monitors are qualified according to ICH-GCP and DIN ISO 14155 and follow the CRO’s SOPs MON 002, 003, 007, and 008. On-site monitoring starts with a pre-trial visit to each center in order to ensure that each center is capable of complying with the study protocol and recruiting an adequate number of patients. The findings of the pre-trial monitoring visit will be summarized in a report, which will be forwarded to the PI and the steering committee. The monitoring will follow a risk-based approach, and the study will be considered a low-risk trial. Thus, 100% source data verification focuses on informed consent, inclusion/exclusion criteria, adverse events of special interest, the primary endpoint, and randomization. All other aspects of the trial are subject to a 20% source data verification. In addition to the pre-trial visit, on-site monitoring is scheduled at the beginning (initiation visit) and at the end of the study (closeout visit), and at months 6, 12, and 24.

### Stopping rules

For patients: As guaranteed prior to study inclusion, the individual patient will be excluded from study participation if the patient withdraws his or her informed consent. Other stopping rules for patients are not applicable due to the single-day character of the trial intervention.For participating centers: Recruitment and protocol-compliant implementation of the follow-up examinations will be monitored by the DSMB throughout the entire trial period. If recruitment at the 50% landmark is less than 20% of the total target number of patients, the enrolling center will have to be excluded from participating in the trial.For the entire trial: If recruitment in more than one center is not possible, the Trial Steering Committee will be consulted to determine whether continuation of the trial is still realistic. If the incidence of adverse events of special interest with the trial intervention is significantly higher than that in the control group (> 50% more complications), continuation of the trial must be discussed with the DSMB and the Trial Steering Committee.

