## Methods: participants, interventions and outcomes

### Study setting

The trial will be conducted at five German medical centers with high expertise in shoulder surgery. All investigators are shoulder surgeons certified by the German, Austrian, and Swiss Society for Shoulder and Elbow Surgery (DVSE) and renowned experts in the field. In preparation of the trial, participating centers had to provide the average number of potentially eligible patients using hospital data management systems and ICD-10 codes of the included pathologies (M75.2, M75.6, S43.4, S46.1, S46.2) over the past 5 years to ensure access to the relevant target population and site capability. Capability of recruitment and recruitment progress by predefined milestones will be independently monitored by a CRO for all centers. All investigators and observers at each study site were trained in ICH-GCP E6 (R2) guidelines prior to study initiation.

The following centers met the selection criteria and have agreed to participate in the conduct of the trial: Department of Trauma Surgery, University Hospital Regensburg; Center for Musculoskeletal Surgery, Charité Berlin; Department of Shoulder Surgery, Vivantes Auguste-Viktoria-Clinic Berlin; Department of Trauma Surgery, Hand Surgery and Sports Medicine, St. Vincentius Clinic Karlsruhe; Sporthopeadicum Regensburg/Straubing.

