#### Trial flow

One hundred ninety-two patients (*n* = 96 for experimental group, *n* = 96 for standard-of-care group) with LHB tendon disorders meeting all eligibility criteria will be randomized equally to implant-free loop tenodesis or arthroscopic epiosseous anchor tenodesis of the LHB tendon. The overall trial flow and timeline for data collection is outlined in Fig. 1.

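### The center-exclusion rule sets its bar at 20% of the trial's total target, which five centers cannot all meet; read literally, an on-schedule trial would lose at least three of them

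*Protocol article*

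**What the plan says.** The protocol article, section Stopping rules, has one rule for participating centers, which begins "If recruitment at the 50% landmark is less than 20% of the total target number of patients, the enrolling center" and ends in that center's exclusion. The exclusion is from participation in the trial, and it is mandatory.

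Three other statements bear on it:

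- **Target.** Trial flow gives "One hundred ninety-two patients" as the number to be randomized, and Sample size calculation gives the same total. No target for a single center is printed.
- **Centers.** Study setting: "The trial will be conducted at five German medical centers".
- **Trial-level rule.** The next sentence of Stopping rules reads "If recruitment in more than one center is not possible, the Trial Steering Committee will be consulted", to judge whether going on is realistic.

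The article does not say whether the 50% landmark means half of the patients or half of the recruitment period. Study setting and the section on the coordinating center and DSMB both mention recruitment milestones, but neither prints them.

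**The concern.** A bar for one center should be measured against what one center is expected to deliver. This one is measured against the whole trial. With five centers, 20% of the total is exactly one equal share of the complete trial, so the rule asks each center to have delivered its full equal share when only half of the recruitment is due. A center exactly on plan would fail.

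Two things are at stake. The first is a monitoring rule that the DSMB cannot apply as written, because doing so would remove most centers from a trial that is recruiting normally. The second is the status of patients already randomized at an excluded center. On the planned 12-month recruitment period, nobody has reached the 12-month visit at the halfway date, so every primary-endpoint value from such a center would still be outstanding.

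**Working it through.** **Inputs.** Total target 192 (Trial flow; Sample size calculation). Centers: 5 (Study setting). Bar: 20% of the total target (Stopping rules). Recruitment from December 2024 to November 2025, 12 months (Trial status). Reference center: 55 patients in 7 months in the pilot study (Discussion).

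**1. The plan's own total.** With margin 5, SD 10, true difference 0, one-sided 2.5% and 90% power, the noncentral t calculation gives 86 per arm, or 172 in total (power 0.903). Allowing for 10% drop-out, 172 / 0.90 = 191.1, which becomes 192 for equal arms. The target reproduces and is not in question.

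**2. The bar.** 0.20 × 192 = 38.4, so a center needs at least 39 patients.

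**3. Landmark at half of the patients.** 192 / 2 = 96 enrolled. 96 / 39 = 2.46, so at most two centers can pass and at least three of five fail. With even recruitment each center has 96 / 5 = 19.2, half of the bar, and all five fail.

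**4. Landmark at half of the recruitment period (month 6).** On-schedule recruitment again gives 96. For other totals, the largest number of centers that can pass is the whole part of (enrolled / 39):

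| Enrolled at landmark | Most centers that can pass | Fewest excluded |
|---|---|---|
| 78 to 116 | 2 | 3 |
| 117 to 155 | 3 | 2 |
| 156 to 192 | 4 | 1 |

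The thresholds are 2 × 39 = 78, 3 × 39 = 117 and 4 × 39 = 156. Below 78, even fewer can pass. Reaching 117 means running 117 / 96 = 1.22, about 22% ahead of plan. Five passing centers would need 5 × 39 = 195, more than the whole trial.

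**5. With the article's own recruitment figure.** At the pilot rate the reference center enrolls 55 / 7 × 6 = 47 in six months and passes. The other four share 96 − 47 = 49, so at most one more can reach 39.

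**6. Other denominators.**

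- 172 evaluable patients: 0.20 × 172 = 34.4, so 35 per center. 96 / 35 = 2.74, still at most two.
- 20% of the 96 already enrolled: 19.2, so 20 per center. 96 / 20 = 4.8, at most four.
- The center's own target, assuming equal shares of 192 / 5 = 38.4: 0.20 × 38.4 = 7.7, so 8 patients against 19.2 expected. All five can pass.

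Of these readings, only the last lets all five centers pass.

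**The case against.** The strongest reply is that the rule sits under the heading for centers and speaks of the enrolling center, so the total target may mean that center's full target as opposed to its halfway figure. The rule then works, and the absurd literal result is itself a sign that it was not meant. Center figures may also exist among the milestones that the article does not print. This stands as a reading of intent, and it is probably right. It does not rescue the text: the sentence names the total target number of patients, and the only such number in the article is 192.

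It also stands that the count of three depends on the landmark, as the table shows.

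Three stronger inferences are tempting, and the article does not support them.

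- **Patients already randomized would be lost.** Nothing in the rule removes them. Statistical methods defines the primary population as all randomized patients with at least one LHB score, without an exception for excluded centers, and Trial status plans 24 months of follow-up for everyone. What remains is a risk from wording that excludes the center from the trial rather than from new enrolment.
- **The randomized comparison would be broken.** Randomization is blocked within center. Removing a whole center for slow enrolment leaves the comparison intact within each remaining center. Precision and generalizability could suffer.
- **The trial-level rule would follow automatically.** That rule concerns centers where recruitment is not possible, which is more than slow, and it leads only to consultation.

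**Conclusion.** The rule is wrong as written. Against the only stated target, it demands 39 patients from each center at the 50% landmark. At least three of five centers fail with 96 enrolled, and all five if recruitment is even. Under a calendar landmark, at least three fail up to 116 enrolled, then two or one; at no enrolment up to 192 is it zero.

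This rests on taking the total target as 192 and applying the bar to each center separately, which is what the sentence says. If each center's own target was meant, the defect is an unstated denominator and the rule is workable.

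The point should be fixed before the landmark is assessed, but it is an operational matter. The hypothesis, margin, sample size, estimands and analysis model are unaffected, and a sensible committee would probably not apply the literal rule.

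**What to change.** Amend the center rule to do three things:

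1. Express the bar as a percentage of each center's own planned number, and state or refer to those numbers.
2. Define the 50% landmark as either half of the recruitment period or half of the patients.
3. State that a center below the bar is closed to new enrolment, and that all patients already randomized there are followed to 24 months and included in the analysis.

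The cost is a one-sentence amendment, passed on through the amendment route that the article already describes. No change to the sample size or the analysis is needed.
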